### Experimental intervention (SOC + COMS)

The COMS device delivers combined photobiomodulation in the red (630–680 nm) and near-infrared (800–860 nm) wavelengths, together with low-intensity pulsed magnetic stimulation at field strengths of 1–100 mT [21]. Each treatment session lasts 16 min and is administered two to three times per week for 8 weeks [21]. The applicator is positioned 2–4 cm above the wound surface without direct contact. Calibration of light output and magnetic intensity is verified at production.

### Control arm (SOC only)

Participants receive optimized SOC identical to the experimental arm but without COMS treatment.

### Criteria for discontinuing or modifying interventions

Treatment discontinuation or modification will occur:Under emergency circumstances, based on his/her clinical judgment, the principal investigator at site may proceed to deviations from the CIP or study discontinuation to protect the rights, safety and well-being of the subjects, without prior approval by the Sponsor and the CEC. AEs related to the IMD and all SAEs must be reported and participants followed up until resolution of the event.If the scientific integrity of the investigation is compromised (noncompliance with the clinical trial protocol or GCP requirements from the part of the subject, the investigator, or the trial staff).If the participant decides to withdraw from the study.

### Strategies to improve adherence to interventions

When the intervention is under medical control, compliance is warranted. Device applications will be documented by clinical staff in the site device accountability log. When the intervention is performed in the homecare setting, participants will receive education on the rationale for session frequency, and the participant will be asked to complete a treatment diary. The planned treatment course consists of 24 sessions; completion of at least 16 sessions is considered the minimum exposure required to assess adherence, a minimum of 16 treatments. In case treatment sessions are missed, these can be made up in the 4-week follow-up.

### Relevant concomitant care permitted or prohibited

SOC compression and wound dressings are permitted; antimicrobial dressings may be used for local infection. Use of photosensitizing agents or medications and drug immunosuppression are prohibited. Arterial interventions, venous interventions, cell and tissue-based therapies (such as skin grafts), and advanced wound care therapies (such as negative pressure wound therapy) are prohibited. Concomitant medications and therapies for comorbidities, or any antibiotic treatments administered during the study period are allowed but must be documented accordingly.

### Provisions for post-trial care

Participants completing the study will return to usual clinical follow-up at their site. No post-trial access to COMS is planned, as the device is commercially available. Any adverse events related to the device and all SAEs that occur between the signing of the consent form and the end of the study will be followed up until resolution of the event. Compensation for harm will follow institutional policy and national law.

### Visit schedule

Participants attend visits at screening (week −2), baseline/randomization (week 0), and follow-ups at weeks 2, 4, 6, 8, 10, 12, 16, 20, and 24. Each visit includes ulcer assessment, wound photography, compression therapy documentation, changes in concomitant medications/therapies documentation, economic parameters documentation, and adverse event monitoring. Health-related quality of life and pain (Visual Analog Scale (VAS)) are assessed at baseline (week 0) and after 3 months (week 12). The 24-week visit assesses longer-term healing outcomes and ulcer recurrence.

### Ulcer measurement and photography

Ulcer area will be measured using standardized digital planimetry via the ImitoWound application [24]. Images are taken perpendicular to the wound, with a calibration ruler included in the frame. All wound images are uploaded to the central database for blinded review.

### Permitted and prohibited wound care products

A pre-approved formulary of dressings, including foam, hydrocolloid, alginate, and gelling fiber, is permitted. Antimicrobial dressings (e.g., silver) may be used only if there are clinical signs of local infection. Prohibited therapies during the trial include cell and tissue-based therapies (such as skin grafts, skin substitutes) and advanced wound care therapy (such as negative pressure wound therapy (NPWT)).

### Outcomes

#### Primary outcome

The primary outcome is PWAR at week 12 relative to baseline, measured via standardized planimetry with central blinded review.

#### Secondary outcomes

Secondary outcomes include PWAR and complete wound closure at weeks 4, 8, 12, 16, 20, and 24; time to 50%, 90%, and 100% wound area reduction; pain intensity (VAS) and health-related quality of life (Wound-QoL questionnaire) [25] at baseline (week 0) and after 3 months (week 12); ulcer recurrence within 24 weeks in participants whose ulcers achieve complete closure; healthcare resource utilization (dressings, debridement, consultations and COMS One applications); and device adherence and usability in the intervention arm.

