## Introduction

### Background and rationale

Chronic leg ulcers (LU), particularly venous leg ulcers (VLUs), represent one of the most prevalent and persistent forms of lower extremity ulceration [1], with substantial impacts on patients’ physical health, quality of life, and economic well-being [2, 3]. VLUs account for up to 80% of all lower extremity ulcers and remain a leading cause of chronic wound care needs worldwide [4]. The global pooled point prevalence in the general population is estimated at 0.32% (95% CI, 0.11–0.60), and the annual incidence at 0.17% (95% CI, 0.08–0.29) [5]. Prevalence increases markedly with age, with older adults, particularly those aged ≥ 65 years, disproportionately affected. Recurrence is frequent, with up to 76% of patients experiencing ulcer recurrence within one year of healing, underscoring the chronic and relapsing nature of the condition [6].

The epidemiology of VLUs varies across regions, reflecting differences in population demographics, comorbidity profiles, and health system structures. High-income countries report prevalence rates between 0.1% and 0.6% in the general population, with rates exceeding 2% among individuals over 80 years of age [7]. Risk factors for recurrence include persistent venous reflux, inadequate compression maintenance, obesity, reduced mobility, and poor adherence to treatment regimens [3, 8]. Peripheral arterial disease (PAD) further complicates ulcer healing by reducing arterial inflow, leading to a mixed etiology ulcer with poorer prognoses and fewer effective treatment options [7].

The clinical and economic burden of VLUs is considerable, with estimated annual direct medical costs of approximately $10.73 billion (USD) across the studied geographies, averaging about $5,527 per patient per year for those managed conservatively [9]. In the UK, chronic wounds account for approximately 4% of total National Health Service spending, with VLUs representing one of the most resource-intensive categories [10]. Similar patterns are reported in the USA and Australia [11, 12]. Direct costs include dressings, compression systems, nursing visits, and hospital admissions, while indirect costs, such as work absenteeism, informal caregiving, and early retirement, add substantially to the societal impact [13].

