### Objectives

The primary objective of the NAZARÉ trial is to determine whether SOC plus COMS achieves greater percentage wound area reduction (PWAR) at 12 weeks compared with SOC alone. Secondary objectives are to assess PWAR and complete wound closure at each visit, time-to-healing, pain, health-related quality of life, recurrence, and healthcare resource use over a 24-week period.

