### Participant timeline

Screening (week −2) → Baseline (week 0) → Follow-up visits at weeks 2, 4, 6, 8, 10, 12, 16, 20, and 24.

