### Statistical methods

#### Statistical methods for primary and secondary outcomes

The primary endpoint (PWAR at week 12) will be analyzed using analysis of covariance (ANCOVA) adjusting for baseline ulcer area, ulcer type, and site. Binary outcomes (e.g., complete closure) will be assessed with logistic regression; time-to-event data (e.g., time to 100% closure) with Cox proportional hazards models; and repeated measures with linear mixed-effects models. The significance level is set at *α* = 0.05 (two-sided). Confidence intervals will be reported at 95%. All statistical analyses will be performed using Stata (version 16.1) and R (version 4.3.2).

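### Recurrence is defined only in participants whose ulcer closed and is observed only to trial week 24, so the arms are compared in a non-randomised subgroup with unequal time at risk

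*Protocol article*

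**What the plan says.** The Secondary outcomes section of the protocol article defines recurrence as "ulcer recurrence within 24 weeks in participants whose ulcers achieve complete closure". Three other places fix the observation window:

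- Objectives sets the aim as "recurrence, and healthcare resource use over a 24-week period".
- Visit schedule states "The 24-week visit assesses longer-term healing outcomes and ulcer recurrence".
- Participant timeline counts from baseline: "Follow-up visits at weeks 2, 4, 6, 8, 10, 12, 16, 20, and 24". No visit follows week 24.

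The trial also tests whether the device speeds healing, through complete closure at several visits and "time to 50%, 90%, and 100% wound area reduction". The statistical methods section reads "Binary outcomes (e.g., complete closure) will be assessed with logistic regression; time-to-event data (e.g., time to 100% closure) with Cox proportional hazards models". Recurrence is named under neither model. The only recurrence rate given is in Background and rationale: "up to 76% of patients experiencing ulcer recurrence within one year of healing".

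**The concern.** Two features of the definition matter, and they are separate.

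1. **The denominator is formed after randomisation.** Closure is an outcome that COMS is intended to change. The closed ulcers on COMS and the closed ulcers on SOC are therefore not comparable by virtue of randomisation.
2. **Time at risk depends on when the ulcer closes.** Observation stops at trial week 24 for everyone. An ulcer closed at week 8 is watched for 16 weeks, and one closed at week 16 for 8 weeks. A simple proportion recurring by week 24 ignores this difference.

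Recurrence is a stated objective, and the article stresses how often these ulcers relapse. A difference in recurrence between arms will be read as evidence on the durability of healing under COMS. On this definition it could show a difference where the true recurrence rate is equal, or hide a real one.

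**Working it through.** The article gives no expected recurrence proportion for the trial, so there is no figure of its own to reproduce. The check asks what the defined measure shows when the true recurrence hazard after closure is the same in both arms.

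**Inputs from the article:** end of observation at week 24; recurrence of up to 76% in the year after healing, used as an upper value; 61 participants per arm (Sample size).

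**Assumed, because the article gives none:** lower recurrence rates of 50% and 25% per year; constant hazards; the closure weeks and closure rates shown below.

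**Step 1. Weekly recurrence hazard.** r = −ln(1 − annual rate)/52. For 76%: −ln(0.24)/52 = 0.0274. For 50%: −ln(0.50)/52 = 0.0133. For 25%: −ln(0.75)/52 = 0.0055.

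**Step 2. All closures in an arm at one week (extreme illustration).** Recurrence by week 24 = 1 − exp(−r × (24 − closure week)).

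- At 76% per year, closure at week 8 gives 1 − exp(−0.0274 × 16) = 35.5%. Closure at week 14 gives 1 − exp(−0.0274 × 10) = 24.0%. The spurious difference is 11.5 points.
- Closure at week 10 versus week 16 gives:

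| Annual recurrence | Week 10 (14 weeks at risk) | Week 16 (8 weeks at risk) | Difference |
|---|---|---|---|
| 76% | 31.9% | 19.7% | 12.2 points |
| 50% | 17.0% | 10.1% | 6.9 points |
| 25% | 7.5% | 4.3% | 3.2 points |

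**Step 3. Closure times spread out.** Take a constant closure hazard c = −ln(1 − p)/24, where p is the proportion closed by week 24, and multiply c by a closure hazard ratio for COMS. Among closers, the share recurring by week 24 is

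1 − c × (exp(−24r) − exp(−24c)) / [(c − r) × (1 − exp(−24c))].

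Worked case, with 40% SOC closure, closure hazard ratio 2 and 76% per year:

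- SOC: c = 0.0213, giving 28.8% recurrence and mean time at risk 13.0 weeks.
- COMS: c = 0.0426, closure 64%, giving 30.7% recurrence and mean time at risk 14.0 weeks.
- Spurious excess on COMS: 1.9 points.

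For SOC closure of 30% to 50% and closure hazard ratios of 1.5 to 3, mean time at risk is 12.7 to 13.4 weeks on SOC and 13.1 to 15.9 weeks on COMS. The spurious excess on COMS is:

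- 0.7 to 4.9 points at 76% per year
- 0.4 to 2.8 points at 50% per year
- 0.2 to 1.3 points at 25% per year

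Across these settings, COMS would need a true recurrence hazard ratio of about 0.82 to 0.97 merely to look equal.

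**Step 4. A case in the other direction.** Suppose SOC closes 30% of ulcers at week 10 (14 weeks at risk). COMS closes the same 30% at week 10 and a further 20% at week 19 (5 weeks at risk). Mean time at risk on COMS is (30 × 14 + 20 × 5)/50 = 10.4 weeks, against 14 on SOC. At 76% per year, 5 weeks at risk gives 1 − exp(−0.0274 × 5) = 12.8%. COMS then shows (30 × 31.9 + 20 × 12.8)/50 = 24.3% recurrence, against 31.9% on SOC. The artefact now favours COMS by 7.6 points.

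**Step 5. The same data counted in all randomised participants.** In the worked case of Step 3, closed and recurrence-free at week 24 is 0.40 × (1 − 0.288) = 28.5% on SOC and 0.64 × (1 − 0.307) = 44.3% on COMS. The measure among closers points slightly against the device. The measure among all randomised points towards it.

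**The case against.** **The model is not stated.** A reader might infer that recurrence, being yes or no, will go into the logistic regression that the article plans for binary outcomes. The article does not say so. Cox regression timed from closure and censored at the last visit would fit the stated methods, and the choice may sit in an analysis plan that is not shown. This stands: it cannot be said that unequal time at risk will be ignored. But Cox regression would cure only that part. The restriction to closed ulcers is in the outcome definition itself, and no choice between these two models removes it.

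**The direction is not fixed.** A reader might infer that the comparison is biased against COMS. Step 4 shows that this fails if COMS converts non-closers into late closers. Selection can also act either way, for example if COMS closes harder ulcers that recur more. This stands in full.

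**The size is modest.** The differences of about 12 points need the upper-bound recurrence rate and a single closure week per arm. With 61 per arm, the worked case gives about 24 and 39 closers (0.40 × 61 and 0.64 × 61). The standard error of the difference is then √(0.288 × 0.712/24 + 0.307 × 0.693/39), about 12 points, so a spurious excess of 0.2 to 5 points would sit well inside the noise. This too stands, and it limits the practical weight of the point.

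**Much of the remedy may already be there.** Complete closure at week 24 is a listed secondary outcome. If it is scored by status at that visit, a reopened ulcer is already a failure, except one that recurs and closes again before week 24. This is largely right, but the article does not link the two outcomes.

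**Closed ulcers are the natural population for recurrence.** An ulcer that never closed cannot recur. That justifies describing recurrence in closers, but it does not make the contrast between arms a randomised one.

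**The window could mean 24 weeks after closure.** The last visit is at trial week 24, so that reading could not be observed under the schedule for an ulcer that closes after baseline.

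**Conclusion.** The point holds for the definition. Recurrence is assessed in a subgroup selected by an outcome that the device is meant to change, and time at risk is 24 minus the closure week. A between-arm difference on that basis is not a randomised comparison of durability.

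If COMS mainly brings closure forward and recurrence hazards are equal, a simple proportion overstates recurrence on COMS by about 0.2 to 5 points. That range rests on constant hazards, 25% to 76% annual recurrence, 30% to 50% SOC closure by week 24 and closure hazard ratios of 1.5 to 3. Only the 76% comes from the article, and there it is an upper value. About 12 points is an extreme illustration, not an expectation.

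The documents do not support two stronger conclusions: that the bias must run against COMS, or that logistic regression is the planned analysis. This is one secondary outcome, and the primary endpoint and sample size are untouched. It is worth correcting because the correction is cheap.

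**What to change.** 1. Make the between-arm durability outcome closed and recurrence-free at week 24 among all randomised participants. State how it relates to the existing week 24 closure outcome, and count ulcers that reopened as failures, including those that closed again. Say that this outcome combines healing with durability and does not isolate recurrence.
2. Report recurrence among closed ulcers as time from closure to recurrence, censored at the last visit, and label it descriptive and non-randomised.
3. State that the 24-week limit is trial week 24 from baseline, not 24 weeks from closure.

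The visits and wound images are already planned, so nothing is added for participants. The cost is minor rewording, one additional analysis and, as a change to an outcome, notification under the article's own amendment procedure. Completion is anticipated in December 2027, which leaves time to settle the definition before the data are analysed.

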#### Safety outcomes

All serious adverse events (SAEs) will be reported. Only adverse events (AEs) related to the investigational medical device (IMD) and not related to the natural course of VLUs evolution will be reported. Severity and connection to the IMD will be categorized according to ISO 14155 definitions.

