## Assignment of interventions: blinding

### Who will be blinded?

Due to the visible nature of COMS treatment, participant and clinician blinding is not feasible.

However, blinding will be maintained for outcome assessors, data analysts, and the steering committee. Wound images will be coded using participant’s unique identification numbers, and blinded assessors will review them centrally without knowledge of treatment arm or site. Statistical analyses will be conducted using masked treatment codes until database lock.

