### Adverse event reporting and harms

All serious adverse events (SAEs) will be recorded and reported. Only adverse events (AEs) deemed device-related will be reported to authorities. Severity and causality will be graded per ISO 14155 definitions. Annual safety summaries will be submitted to ethics committees. Investigators will assess and document each (S)AE from onset until resolution.

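### Non-serious adverse events are reported only if judged device-related, so the SOC arm shows none by definition and non-serious harm cannot be compared between arms

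*Protocol article*

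**What the plan says.** The Safety outcomes section of the protocol article has two rules. Serious events carry no causality condition: "All serious adverse events (SAEs) will be reported". Other events must meet two conditions together to be reported: "Only adverse events (AEs) related to the investigational medical device (IMD) and not related to the natural course of VLUs evolution".

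Criteria for discontinuing or modifying interventions repeats the device filter for reporting: "AEs related to the IMD and all SAEs must be reported and participants followed up until resolution of the event". Provisions for post-trial care uses it to set who is followed up: "Any adverse events related to the device and all SAEs that occur between the signing of the consent form and the end of the study".

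Two other sections point elsewhere. Adverse event reporting and harms attaches the filter to one recipient, "Only adverse events (AEs) deemed device-related will be reported to authorities", and has investigators assess and document every event, serious or not, until it resolves. Visit schedule puts adverse event monitoring into each visit and does not limit it to one arm.

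On exposure and blinding, the Control arm section says "Participants receive optimized SOC identical to the experimental arm but without COMS treatment", and Who will be blinded? says "participant and clinician blinding is not feasible".

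**The concern.** A randomised control arm lets harm be judged by comparing rates, without deciding event by event what caused what. A safety outcome that admits a non-serious event only after it has been attributed to the device gives up that advantage, because one arm has no device to attribute anything to.

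The second condition adds to the problem. Local infection, skin reaction around the ulcer and ulcer deterioration are plausible effects of a device applied over the wound. They are also the events most readily put down to the ulcer's own course. Only a comparison with similar ulcers not exposed to the device can separate the two explanations.

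The resulting table could mislead in either direction. It could show an apparent excess against COMS where none exists, or hide a real excess that staff ascribed to the ulcer. The primary analysis is not affected.

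**Working it through.** **Inputs.** 61 participants per group (Sample size); no COMS in the control arm (Control arm); the two-condition rule (Safety outcomes); unblinded clinicians (Who will be blinded?). The protocol gives no adverse event rates, so the rates below are assumed and shown as a range.

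**The plan's own figure.** The 61 per group serves here only as a denominator. With a difference of 20 points, SD 33, two-sided alpha 0.05 and 90% power, the normal approximation gives 2 × (1.960 + 1.282)² × 33² / 20² = 57.2, so 58 per arm. Then 58 × 1.05 = 60.9, so 61 per arm and 122 in total. Nothing in this point disputes that number.

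**Step 1: the control count.** A reportable non-serious event needs device-relatedness. Control participants have no device exposure. The count is 0 of 61 for any true rate.

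**Step 2: the COMS count.** Let p be the true proportion with a non-serious event, equal in both arms, and a the share of COMS-arm events that staff attribute to the device and not to the ulcer. The expected number listed is 61 × p × a.

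| p | a = 25% | a = 50% | a = 100% |
|---|---|---|---|
| 10% | 1.5 | 3.05 | 6.1 |
| 20% | 3.05 | 6.1 | 12.2 |
| 30% | 4.6 | 9.15 | 18.3 |

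The control entry is 0 in every cell, although the true control number is 6.1, 12.2 or 18.3.

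**Step 3: a false signal.** With 61 per arm, a two-sided Fisher test gives p = 0.057 for 5 against 0 and p = 0.027 for 6 against 0. The protocol plans no such test; it is used here as a yardstick. The binomial probability of 6 or more listed COMS events, with no true difference between arms, is:

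| p | a = 25% | a = 50% | a = 100% |
|---|---|---|---|
| 10% | 0.004 | 0.084 | 0.579 |
| 20% | 0.084 | 0.579 | 0.990 |
| 30% | 0.307 | 0.911 | > 0.999 |

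**Step 4: a missed signal.** Suppose the true rates were 30% with COMS and 10% with SOC, about 18 against 6 of 61. If every event were put down to the ulcer (a = 0), the table would read 0 against 0.

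**Step 5: the sections side by side.** Safety outcomes restricts what is reported as the trial's safety outcome. The discontinuation section restricts reporting in the same way. The harms section restricts only what goes to authorities and has all events documented. Visit schedule has monitoring at each visit. A site following the first two could leave control-arm events unreported; a site following the last two would record them. The article does not say which governs.

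**The case against.** A reader might infer that harm cannot be compared at all. The documents do not support that. SAEs are reported in both arms with no causality or ulcer-course condition, and the harms section repeats this, so serious harm remains comparable.

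Several local problems are also captured regardless of attribution. Enlargement would show as negative PWAR, measured at six follow-up times with blinded image review. Pain is compared by VAS. Antibiotic treatments must be documented, and dressings, debridement and consultations are resource outcomes. This stands, and it narrows the point. Three gaps remain:

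- Skin reaction around the ulcer has no other record in the article.
- Infection is visible only indirectly, through treatment records, and is not an outcome.
- After baseline, VAS is taken only at week 12, four weeks after the planned 8-week course ends, so pain during treatment is largely unseen.

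A reader might also infer that control-arm non-serious events will not be recorded. That is not established either. Safety outcomes speaks of reporting, while the harms section and Visit schedule suggest recording in both arms. The article condenses a fuller plan that is not shown, and its safety sentence may be a shortened authority-reporting rule. That possibility is a reason to reconcile the sections. It does not remove the defect, because the restriction appears as the definition of the safety outcome and is repeated elsewhere.

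Finally, this is a post-market study of a CE-marked device that the protocol regards as minimal risk, comparative safety is not a stated objective, and the remark on tolerability in the Discussion is conditional. All of that is fair and limits the seriousness. It does not make a count that is zero by construction interpretable.

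**Conclusion.** The point holds for non-serious adverse events. As the safety outcome is written, the SOC arm contributes 0 of 61 by definition and the COMS count reflects unblinded attribution, so the two cannot be compared. Local infection and surrounding skin reactions are the events most affected.

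The zero follows from the protocol's rules alone. The range of about 2 to 18 listed COMS events rests on assumed true rates of 10% to 30% and attribution of 25% to 100%. That site staff judge relatedness is inferred from the harms section, where investigators assess each event; the blinded central review described in the article concerns wound images.

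Serious harm, wound area and the primary analysis are unaffected. The conflict between Safety outcomes and the discontinuation section on one side, and the harms section and Visit schedule on the other, needs an explicit resolution. This is a worthwhile, low-cost correction and does not threaten the trial's main conclusion.

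**What to change.** Reconcile Safety outcomes and the discontinuation section with the harms section, as follows:

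- Record non-serious adverse events, at least those of the study leg or ulcer, in both arms at the scheduled visits, whatever their presumed cause.
- Report them by arm in all randomised participants, alongside all SAEs, with device-relatedness as a recorded attribute and not as an entry condition.
- Keep the device-related filter only for reports to authorities.

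Present the comparison as estimates with confidence intervals. With 61 per arm, the approximate power is 34% for 10% against 20%, 68% for 20% against 40% and 80% for 10% against 30% (assumed rates), so a non-significant result would not show that the arms are equally safe.

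The cost is a small increase in site recording work. Event monitoring is already part of each visit, and antibiotics and wound areas are already documented. Recruitment began in October 2025 with completion expected in December 2027, so an early amendment could still cover most participants.
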